### Statistics and analysis

3.4

#### Target sample size

3.4.1

A total sample size of 160 patients is planned. For a balanced 4-group trial, approximately 40 patients must be recruited per allocation group (nitrogen group, 50% xenon group, 75% xenon group, and 100% xenon group).

#### Sample size calculation

3.4.2

The sample size calculation is based on the primary outcome measure, which is the variable of OI at perioperative period. Currently, there is no established minimal clinically important difference (MCID) for the OI. Based on previous study,^[17]^ an approximation to the MCID could be viewed as 38 mm Hg, the standard deviation (SD) of a single OI observation as 70 mm Hg, and the auto-correlation as 0.5. With a 5% (2-sided) type I error rate, based on preliminary experiments, 36 patients per treatment group are necessary, and the power was 0.80048. Assuming a 10% dropout rate, the final sample size will be 160 patients (40 patients/group) (Table 2). (Power Analysis and Sample Size, PASS V11.0, NCSS, LLC; Kaysville, UT).

**Table 2 T2:**

Power of calculated sample size.

#### Analysis of endpoints

3.4.3

The statistical analysis of the study is the responsibility of the trial statistician. Baseline data will be compared to determine whether or not there are any clinically important differences between treatment and control groups that have occurred by chance. The analysis will be performed by SPSS statistical software (SPSS for Windows, V.18.0; Chicago, IL).

All statistical testing will be performed at the 2-sided 5% significance level, and 95% confidence intervals will be presented where appropriate. For all analyses, the appropriate model assumptions were verified, and alternative methods used if more appropriate. Prior to any analysis, any missing data patterns will be investigated, the reasons for missing data obtained and summarized where possible. The primary analysis, such as OI, inflammatory cytokines, and ROS, will be conducted on the repetitive measurement and analysis of variance. The intubation time will be summarized descriptively using median, interquartile ranges and ranges overall, as well as by treatment arm. Complications between the trial arms will be compared in terms of frequency and severity. Cross-tabulations will be generated to relate complications to treatment, and chi-squared tests will be used to assess the significance of the association. A receiver operating characteristic (ROC) curve will be used to test discrimination of the treatment model. A *P* value <.05 will be considered statistically significant.

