### Follow-up and end of study definition

3.3

After 3, 6, or 12 months, the participant will be consulted in out-patient department or contacted by telephone for assessment of individual survival, living condition, and major adverse events. The whole duration of the study will be 1 year and will end after the 1-year follow-up of the last patients. Participants have no obligation to complete the whole study and they are free to decide to withdraw at any point.

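### Classical repeated-measures ANOVA discards the recorded end-of-surgery OI of any patient without a 6-hour value, which wastes data and may bias the xenon effect in either direction

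*Protocol article*

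**What the plan says.** Section 2.4.1 defines the primary outcome as the perioperative change in OI over three times: before surgery, at the end of surgery and 6 hours after it. Section 2.4.2 sets four times, to 24 hours, for cytokines and ROS. Section 3.4.3 names SPSS 18 and states that the analysis of OI, cytokines and ROS "will be conducted on the repetitive measurement and analysis of variance".

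On incomplete data, section 3.4.3 says that patterns and reasons will be examined and summarised before analysis. It also lets other methods be substituted, in a sentence about checking model assumptions. It gives no rule for a patient with some but not all values.

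Section 3.4.2 handles loss by adding patients: "36 patients per treatment group are necessary, and the power was 0.80048", and then "Assuming a 10% dropout rate, the final sample size will be 160 patients (40 patients/group". Section 3.3 adds: "Participants have no obligation to complete the whole study and they are free to decide to withdraw at any point". Section 4.2 puts dropout at 10% to 15% over the whole study, which follows patients to 12 months.

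**The concern.** Classical repeated-measures ANOVA (the GLM repeated-measures procedure in SPSS) needs a complete set of values per patient. A missing 6-hour OI therefore removes the presurgery and end-of-surgery values too, although both may have been recorded. Section 4.1 reports that in the earlier non-randomised study 50% xenon lessened the fall in OI at the end of surgery and that the effect had faded by 6 hours. The deletion thus falls on the time point where an effect is most expected.

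Loss in this window need not be random. The 6-hour value comes soon after major aortic surgery, and section 2.9.3 ties OI to fixed ventilator settings. A patient who has died has no value, and one already extubated cannot be measured under those settings. The first kind of loss would tend to remove poor oxygenation and the second good oxygenation. Extubation time is itself a secondary outcome, so treatment could affect who is missing. Recruiting extra patients protects power but not against bias of this kind.

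**Working it through.** **Inputs from section 3.4.2.** The difference: "an approximation to the MCID could be viewed as 38 mm Hg". The SD: "the standard deviation (SD) of a single OI observation as 70 mm Hg". The correlation: "and the auto-correlation as 0.5". Alpha is 5% two-sided, with 36 evaluable and 40 recruited per group.

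**The plan's own figure.** For the mean of three equally correlated values, the variance factor is (1 + 2 × 0.5)/3 = 0.667, so the SD of the mean is 70 × √0.667 = 57.15. With 36 per group, power = Φ(38/(57.15 × √(2/36)) − 1.96) = 0.805 (0.794 with the t distribution), close to the stated 0.80048. Inflation is 36/0.90 = 40, as stated. (As a separate matter, 0.80048 is met exactly by 40 per group with two values, factor 0.75.) With three values, power is 0.845 with 40 complete cases per group, 0.826 with 38, 0.805 with 36 and 0.783 with 34. Deletion up to the planned 10% is therefore covered for power. The open question is bias.

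**Bias: assumptions.** The documents give no loss by 6 hours, so I assume 0% to 15% per arm. The true difference is 38 at both postoperative times, the SD is 70 and all correlations are 0.5. Only the 6-hour value goes missing, with a probability that depends on end-of-surgery OI.

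**Formula.** Let e be the amount by which the mean end-of-surgery OI of completers exceeds that of all patients in the arm. The complete-case difference is 38 + e(xenon) − e(control) at the end of surgery. At 6 hours it is 38 + 0.5 × [e(xenon) − e(control)].

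**Graded loss**, where the log-odds of missing rise by 1 per SD of lower OI. At that strength e is 1.69 at 2.5% loss, 3.30 at 5%, 6.35 at 10% and 9.28 at 15% (numerical integration):

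| Loss control / xenon | End-of-surgery difference | 6-hour difference |
|---|---|---|
| 5% / 5% or 10% / 10% | 38.0 | 38.0 |
| 5% / 2.5% | 38 + 1.69 − 3.30 = 36.4 | 37.2 |
| 10% / 5% | 38 + 3.30 − 6.35 = 34.9 | 36.5 |
| 15% / 5% | 38 + 3.30 − 9.28 = 32.0 | 35.0 |
| 5% / 10% | 38 + 6.35 − 3.30 = 41.1 | 39.5 |

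A simulation with 1,000,000 patients per arm agrees for the end-of-surgery difference (36.4, 34.9, 32.0 and 40.9 for the last four rows). If loss is unrelated to OI, e = 0 and the result is 38 even at 10% / 5%.

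**One mechanism in both arms.** If the same graded rule acts on actual OI in both arms and xenon truly adds 38, loss becomes unequal by itself (10% in control, about 6% in xenon) and the estimate is 35.8.

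**Worst-case cutoff.** Suppose every patient below the control 10th percentile, and nobody else, misses 6 hours. In control, e = 70 × φ(−1.282)/0.90 = 13.65. In xenon the cutoff lies at −1.282 − 38/70 = −1.824, loss is 3.4% and e = 5.47. The difference is 38 + 5.47 − 13.65 = 29.8 at the end of surgery and 33.9 at 6 hours. Cutoffs at 5% and 15% give 33.0 and 27.3 at the end of surgery.

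**Change from presurgery.** If the contrast is the change from presurgery, completers' presurgery means also shift, by half of e. The end-of-surgery bias is then halved: 10% / 5% gives 38 − 0.5 × 3.05 = 36.5.

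**Keeping all observed values.** In the simulation, the end-of-surgery difference returned to about 38 in every pattern, and the 6-hour difference to between 37.7 and 38.1. This follows from the set-up, because loss was made to depend only on an observed value.

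**The case against.** The strongest reply is that the protocol never mentions listwise deletion. Its wording is loose, the article is condensed, other methods are permitted, and rules for incomplete records usually sit in an analysis plan that is not shown. Part of this stands: deletion is a consequence of the named method in its usual form, not a stated rule. But the document does name the method. Its permission to substitute another one concerns model assumptions, and examining missing-data patterns does not return deleted values to the analysis.

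Three stronger readings are tempting and are not supported:

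- **That the xenon effect is certainly biased.** Bias needs loss that is related to OI and differs by arm. The documents show neither, and the direction could be either way. Under a single mechanism acting on actual OI, no xenon effect means no unequal loss, so that mechanism weakens a true effect and does not create a false one.
- **That 10% of patients, 16 of 160 with 32 recorded values, will be thrown away.** The 10% to 15% in section 4.2 covers the whole study, and loss by 6 hours may be much smaller. Even the 10% cutoff pattern above loses only about 0.10 × 40 + 0.034 × 120 = 8 patients.
- **That dropouts are meant to leave the analysis.** Inflating 36 to 40 is routine and does not define an analysis set.

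It is also fair to say that a mixed model is no cure if loss depends on the unseen 6-hour state, and that for a death it implies an OI that does not exist.

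**Conclusion.** The point holds in conditional form. The named primary analysis, run classically, excludes partial records and so discards recorded end-of-surgery OI values. The same applies to cytokines and ROS over their four times, although that part has not been quantified. The possible bias in the end-of-surgery difference runs from nil, through about −3 mm Hg (10% / 5%) or +3 mm Hg (5% / 10%), to about −8 mm Hg under the 10% worst-case cutoff, against a true 38. All of this rests on assumed loss rates and an assumed link between loss and OI. Power is not the problem at the planned 10%. The change should be made because it is nearly free, not because bias has been shown.

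**What to change.** In section 3.4.3, replace repeated-measures ANOVA for OI, cytokines and ROS with a linear mixed model for repeated measures (SPSS MIXED) that uses every observed value from all randomised patients in their allocated arm. Report missing 6-hour OI values by arm and reason. State that the model assumes data missing at random and that it does not by itself resolve deaths before 6 hours. A sensitivity analysis that ranks such deaths as the worst outcome may be added.

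The cost is a few sentences and slightly more analysis work in the same software, with no new data or patients.

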#### Primary outcome measure

2.4.1

The study primary outcome measure is the perioperative change of the patient's oxygenation index (OI) presurgery, at end of surgery, and at 6 hours postsurgery. The oxygenation index is calculated by the arterial oxygen tension (PaO_2_)/inspired oxygen fraction (FiO_2_) ratio, and is a validated and effective measure of oxygen impairment change.

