#### Randomization

2.6.2

After written informed consent is obtained and patient eligibility confirmed, patients will have a baseline assessment. They will then be randomized into the study. Patients will be given a study number and randomized on a 1:1:1:1 basis to receive 1 of the 3 treatment options or no treatment (control group). Randomization will be performed using an automated, computer-generated randomized digital table to ensure that all 4 groups are well balanced for the patient characteristics.

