### Intervention content

4.1

The intervention content for each of the groups was carefully selected. The content of the oxygen group was chosen to represent current practice for this operation. Based on a previous non-randomized controlled clinical trial,^[17]^ pulmonary static inflation with 50% xenon during CPB attenuated OI decreases at the end of surgery; but the effectiveness diminished at 6 hours after surgery and the valid intra-alveolar xenon concentration was only about 25% to 30% of the inhaled 50% xenon concentration. Therefore, a xenon-treatment arm was designed as 3 groups of pulmonary static inflation with 50%, 75%, and 100% xenon, respectively. We suggest that future trials might define appropriate concentration of xenon for the best practice intervention.

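### The primary repeated-measures ANOVA of OI treats the presurgery value as an outcome time and names no tested term; using that value as a covariate would gain power at no cost

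*Protocol article*

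**What the plan says.** Section 2.4.1 defines the primary outcome as "the perioperative change of the patient's oxygenation index (OI) presurgery, at end of surgery, and at 6 hours postsurgery". Section 3.4.3 says that the analysis of OI, together with cytokines and ROS, "will be conducted on the repetitive measurement and analysis of variance". It does not say whether the group main effect, the group-by-time interaction or some other contrast decides the result, and it names no covariate. The natural reading is that presurgery OI is one of three levels of the time factor.

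Section 2.6.2 puts the baseline before allocation: "patients will have a baseline assessment. They will then be randomized into the study". Section 3.4.2 gives the planning inputs: "an approximation to the MCID could be viewed as 38 mm Hg", "the standard deviation (SD) of a single OI observation as 70 mm Hg", an autocorrelation of 0.5 and a two-sided 5% error rate. It arrives at 36 per group with power 0.80048, raised to 40 per group for 10% dropout.

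**The concern.** A value taken before treatment has an expected group difference of zero. As an outcome time it adds nothing to the treatment contrast. In a group main effect it pulls the average difference towards zero. In the group-by-time interaction it serves as the reference level, and the test spreads over several degrees of freedom. In neither case is it used for what it does best, which is to predict the postoperative values and remove variance.

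Power matters here because section 4.3 attaches a strong conclusion to a negative result: if no xenon concentration beats nitrogen, use of xenon for this condition should end. A needlessly weak primary test makes a false negative more likely. Leaving the tested term open also means that the planned power is not tied to any particular test.

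**Working it through.** **Inputs** (section 3.4.2): difference 38 mm Hg, SD 70, correlation 0.5, two-sided alpha 0.05, 36 per group (40 if nobody is lost).

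**Assumptions not in the protocol:** the correlation is the same between all pairs of times (compound symmetry); the 38 mm Hg applies at both postoperative times; the expected difference presurgery is zero; two groups are compared at a time, without multiplicity adjustment.

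For single contrasts, power = Φ(difference/SE − 1.96), with SE = SD × √(2/n).

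**The plan's own figures.** The SD of a mean of m times is 70 × √((1 + (m − 1) × 0.5)/m).
- Three times, full 38 at every time: SD 57.15, SE 13.47, power Φ(2.82 − 1.96) = 0.805 at 36 per group, and 36 is the smallest n that reaches 80%. This reproduces the sample size.
- Two times: SD 60.62, power 0.758 at 36 and 0.80048 at 40 per group. This reproduces the printed power to five decimals. Postoperative mean minus presurgery has the same SD and fits equally well.

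The n of 36 and the power of 0.80048 therefore seem to come from different runs. Section 3.4.2 does not settle which test was planned. Table 2 might, but its contents were not available for this check.

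**Candidate analyses at 36 per group:**
- *Group main effect over three times.* Difference (0 + 38 + 38)/3 = 25.33; SD 57.15; SE 13.47. Power Φ(1.88 − 1.96) = 0.468.
- *Group-by-time interaction, two groups.* Noncentrality = (36/2) × (38²/4900) × (1/0.75) = 7.07. With a noncentral F on 2 and 140 df, power is 0.650.
- *Change from baseline* (postoperative mean minus presurgery). Variance factor 0.75 + 1 − 2 × 0.5 = 0.75; SD 60.62; SE 14.29. Power Φ(2.66 − 1.96) = 0.758.
- *Postoperative mean adjusted for presurgery OI.* Variance factor 0.75 − 0.5² = 0.50; SD 49.50; SE 11.67. Power Φ(3.26 − 1.96) = 0.903.

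| Analysis | 36/group | 40/group | 36/group, AR(1) |
|---|---|---|---|
| Group main effect | 0.47 | 0.51 | 0.50 |
| Group-by-time interaction | 0.65 | 0.70 | 0.55 |
| Change from baseline | 0.76 | 0.80 | 0.63 |
| Baseline-adjusted postoperative mean | 0.90 | 0.93 | 0.84 |

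The AR(1) column takes 0.5 between adjacent times and 0.25 between presurgery and 6 hours. With compound symmetry and a correlation between 0.3 and 0.7, the main effect has power 0.56 to 0.40 and the adjusted mean 0.87 to 0.97. The adjusted analysis had the highest power in every case examined.

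Four-group omnibus tests give the same picture. With one arm differing from the other three by 38 mm Hg, power is 0.453 for the main effect, 0.663 for the interaction and 0.925 for the adjusted mean.

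**The case against.** The strongest reply is that the protocol never says it will test the main effect. Its outcome is worded as a change, which fits the interaction or a change-from-baseline contrast better, and the printed 0.80048 equals the power of the change contrast at 40 per group. This stands. A reader might infer that the planned analysis roughly halves the power (0.47 against 0.90), but that holds only for the main effect and under compound symmetry. For the interaction the loss is about a quarter (0.65/0.90 = 0.72), and for the change contrast about a sixth (0.76/0.90 = 0.84).

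Section 3.4.3 also says that "the appropriate model assumptions were verified, and alternative methods used if more appropriate", and covariates may be set in an analysis plan that is not shown. But the clause is about model assumptions, and the loss of power arises even when every ANOVA assumption holds. The article does state a method, and that method is what is reviewed here.

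Two further inferences are tempting and not supported:
- *That ANOVA would delete 10–15% of patients, mainly those who deteriorate early.* Section 4.2 gives that rate for the whole study, which is followed to 12 months. No rate is given for OI missing by 6 hours, and no SPSS procedure is named.
- *That a fading effect makes matters worse by a known amount.* Section 4.1 reports that "the effectiveness diminished at 6 hours after surgery" in the earlier 50% xenon study, but gives no size for the difference at 6 hours. Any figure would be invented, and fading would also lower the power of the adjusted analysis.

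**Conclusion.** The concern holds as a matter of efficiency. The stated analysis of OI uses a pretreatment value as an outcome time and leaves the deciding test unnamed. At 36 per group, each test it could lead to has less power (0.47, 0.65 or 0.76) than adjustment for the same value (0.90). With all 40 per group analysed, the change contrast just reaches 0.80 and the adjusted analysis 0.93. With complete data under randomisation, none of these tests is biased or inflates the type I error, so this is a free improvement and not an error that invalidates the plan.

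The sizes rest on the assumed 38 mm Hg at both postoperative times and on the correlation structure, which section 3.4.2 does not state; the ranking does not change under AR(1). They also require that presurgery OI is taken before any study gas. Section 2.6.2 supports this, but section 2.9.3 ties OI to set ventilator conditions, so the exact moment should be stated. The calculation covers OI only, not cytokines or ROS.

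**What to change.** In section 3.4.3, replace the repeated-measures ANOVA for OI as follows:
- Outcomes: OI at end of surgery and at 6 hours.
- Model: a linear mixed model with presurgery OI (taken before any study gas) as covariate, plus group, visit and group-by-visit; or an ANCOVA of the mean of the two postoperative values on presurgery OI and group.
- Primary contrast: the baseline-adjusted mean of the two postoperative values, each xenon group against nitrogen.
- Supportive: the same contrasts at each postoperative time.

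In section 3.4.2, state the number of times, the correlation structure and the contrast that the sample size refers to, and reconcile the 36 per group with the printed power of 0.80048.

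The cost is wording only. Presurgery OI is already collected, the SPSS software already named can fit either model, and no new data or patients are needed.

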### Design of trial

2.2

The trial is a 4-group, parallel, RCT, which has been registered at www.clinicaltrials.gov (Identifier: NCT02468531). By performing 4 2-way comparisons, we will test differences between groups. Patients will be randomized in a 1:1:1:1 ratio. Blinding will be performed for patients, post intervention assessors, statisticians, and investigators.

The null hypothesis for this trial is that there is no difference in protection effects between nitrogen and xenon in patients with postoperative oxygen impairment. The patients who receive nitrogen are the control group in this comparison. If this null hypothesis is rejected, then inhaled xenon may be an effective treatment. If this null hypothesis is not rejected, then inhaled xenon may be ineffective.

However, there is also a need to understand how potential treatment differences are achieved, and/or if different concentrations of inhaled xenon produce similar effects. Further comparisons, including the use of a control intervention, can provide this information.

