#### Secondary outcome measures

2.4.2

The following are the secondary outcome measures: inflammatory cytokines and reactive oxygen species (ROS) presurgery, at end of surgery, at 6 and 24 hours postsurgery; extubation time; and complications. The timing of all assessments is shown in Table 1 as a schedule of events.

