### Definition of serious adverse events

3.1

A serious adverse event (SAE) is any negative medical occurrence, including death, life-threatening injury, an change requiring inpatient hospitalization or prolongation of existing hospitalization or a change that results in persistent or significant disability and/or incapacity.

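### Extubation time, a named secondary outcome, is only summarised descriptively and under a different name, so the plan yields no between-arm comparison of ventilation time

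*Protocol article*

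**What the plan says.** Section 2.4.2 (Secondary outcome measures) ends its list with "extubation time; and complications", after the cytokines and reactive oxygen species.

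Section 3.4.3 (Analysis of endpoints) sets the analyses:

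- For the oxygenation index and the serum markers: "The primary analysis, such as OI, inflammatory cytokines, and ROS, will be conducted on the repetitive measurement and analysis of variance".
- For complications, cross-tabulation by treatment, after which "chi-squared tests will be used to assess the significance of the association".
- For time on the tube: "The intubation time will be summarized descriptively using median, interquartile ranges and ranges overall, as well as by treatment arm".

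Three general sentences also bear on the point. Section 2.2 (Design of trial) states "By performing 4 2-way comparisons, we will test differences between groups". Section 3.4.3 adds "For all analyses, the appropriate model assumptions were verified, and alternative methods used if more appropriate" and, on missing data, "any missing data patterns will be investigated, the reasons for missing data obtained and summarized where possible".

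The article gives neither extubation time nor intubation time a start or an end, and it does not say how a patient who dies before extubation enters the summary.

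**The concern.** The trial asks whether xenon protects the lung. Ventilation time is its continuous clinical outcome that can reach beyond the 6-hour oxygenation index. Section 4.1 (Intervention content) reports that in the earlier non-randomised study the oxygenation benefit had weakened by 6 hours. A later respiratory outcome is therefore one place where a lasting benefit could show, and it is the one secondary outcome for which the plan names no test, effect estimate or interval. Readers would be left to compare four medians by eye, at about 40 patients per arm.

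Two lesser matters come with it. The two names may denote different quantities: patients are intubated before bypass, so a time counted from intubation includes the operation, while a time to extubation may be counted from the end of surgery. And a patient who dies on the ventilator has no extubation time, so the summary depends on a coding choice that the article does not state.

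**Working it through.** **1. Outcomes against analyses.** Taking the secondary outcomes in section 2.4.2 in turn and looking up each in section 3.4.3:

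| Secondary outcome | Analysis fixed | Between-arm comparison? |
|---|---|---|
| Cytokines, reactive oxygen species | Repeated-measures analysis of variance | Yes |
| Complications | Chi-squared tests | Yes |
| Extubation time | Median, IQR and range of intubation time | No |

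Only the last row has no comparison.

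**2. The article's own figure.** It gives no power or sample size for extubation time. Its one power figure is for the oxygenation index, and it reproduces. With SD 70, correlation 0.5 and three measurements, the SD of a patient's mean is 70 × √((1 + 2 × 0.5)/3) = 57.15. With 36 per group, 38 / (57.15 × √(2/36)) = 2.82, and power is Φ(2.82 − 1.96) ≈ 0.805 (0.794 by the t distribution), against 0.80048 stated. Then 36/0.90 = 40 per group, or 160 in all. None of this sizes a comparison of ventilation time.

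**3. How much uncertainty four bare medians hide.** This is an illustration. Assume log-normal times with a log-SD of 0.8, which is not in the article. For a rank comparison of two arms of 40, the standard error in log-SD units is √(2/40) / √(3/π) = 0.229. The difference detectable with 80% power at two-sided 5% is (1.960 + 0.842) × 0.229 = 0.641 log-SD, a ratio of exp(0.8 × 0.641) = 1.67. With 36 per arm the ratio is 1.72. Under this assumption, sizeable differences between two medians are compatible with chance, and the planned summary gives the reader no way to see that.

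**4. Death before extubation.** The article gives no rate of death on the ventilator, so this too is an illustration. Assume a true median of 24 h, a log-SD of 0.8, and 5% to 20% of an arm dying on the ventilator independently of ventilation time. In the early case, death falls at a uniform fraction of the ventilation time the patient would have had. In the late case, it falls at 1.5 to 4 times the median. Arm medians from a simulation of 400,000 patients per setting:

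| Deaths | Early, time ends at death | Late, time ends at death | Deaths ranked worst | Deaths excluded |
|---|---|---|---|---|
| 5% | 23.3 h | 25.4 h | 25.4 h | about 24 h |
| 10% | 22.6 h | 26.8 h | 26.8 h | about 24 h |
| 20% | 21.1 h | 31.0 h | 31.0 h | about 24 h |

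At 20% deaths the shift runs from (21.1 − 24)/24 = −12% to (31.0 − 24)/24 = +29%. The late column equals the worst-rank column because every late death lies above the median. As a check on the worst-rank column at 20%: the median is the 0.5/0.8 = 0.625 quantile of the assumed times, 24 × exp(0.8 × 0.319) = 31.0 h. So the sign depends on when deaths occur and how they are coded.

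**The case against.** The strongest reply is that a descriptive summary of a secondary outcome is a legitimate choice in a trial sized on the oxygenation index. It avoids further tests, the arms are shown side by side with IQR and range, and a separate analysis plan could still name a rank test. Part of this stands. The outcome is secondary, the data are collected either way, and more tests do add to multiplicity. It does not remove the point, because the article does not leave the method open: it chooses one, and an analysis plan that followed it would contain no comparison. The clause allowing alternative methods concerns model assumptions and does not turn a summary into a comparison. The general intention to test differences between groups sits in tension with the summary and does not resolve it.

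On deaths, a reader might infer that the plan counts patients who die on the ventilator as early extubations, so that an arm with more deaths would look better. The document does not support that. It states no rule; dropping such patients as missing is at least as natural a reading; and even if time stopped at death, a death after long ventilation would lengthen the median. Nor does the article predict early loss. Section 3.4.2 allows 10% dropout and section 4.2 allows 10% to 15% over the whole study, neither tied to death or to the ventilated period. The Introduction's remark on high mortality describes the disease in general, while the exclusion criteria remove unstable patients and those with malperfusion. Silence on the handling of death is something an article commonly leaves to the full plan, and it is not counted as a fault here.

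**Conclusion.** The point holds as a minor one. As written, extubation time is the only listed secondary outcome without a between-arm test or estimate, it is analysed under another name, and the summary cannot say whether xenon shortens ventilation. This rests on the text alone and needs no assumption.

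The handling of death matters for the remedy. Whatever comparison is named must say where such patients go, because the median could move either way. The −12% to +29% range at 20% deaths depends wholly on assumed times and death rates, and the true size cannot be derived from the article. No figure in the protocol changes, and the primary outcome is unaffected.

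**What to change.** Use one name throughout and define it, for example as time from the end of surgery to extubation. Compare each xenon arm with nitrogen in all randomised patients by a Mann-Whitney test, giving death before extubation the worst rank. Report a Hodges-Lehmann or median difference with a 95% confidence interval where it can be estimated, and the number of deaths before extubation in each arm. Keep the planned median, IQR and range beside it.

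A competing-risk analysis (cumulative incidence of extubation with death as the competing event, Gray's test) is a reasonable alternative. It is not equivalent: it is a log-rank-type test, the other is Wilcoxon-type, and the two can give different results. Choose one before the data are seen.

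The cost is a little more analysis work and three more comparisons, to be labelled secondary or exploratory. No patients, visits or measurements are added, and the rank test runs in the planned SPSS.
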